##### Cost

What are the costs of implementing the strategy?

## Methods

### Design and ethics

This multi-centre study will use a balanced incomplete block design, consisting of two arms (Figure 1). LQICs will be allocated at random to one of these two arms. All LQICs allocated to arm A will receive the intervention with respect to the clinical topics associated with arm A. All LQICs allocated to arm B will receive the same intervention, but with respect to the topics associated with arm B (table 1). Each arm will have five different CME topics to choose from. Each LQIC will choose three different topics for their discussions, and serve as a control for the other arm. The GPs will not be aware of the topics they are serving as controls for, to avoid the Hawthorne effect [29].

**Table 1 T1:** Modules and distribution over the research arms.

	Modules		
	
	Topic	Examples of tests	Examples of drugs
Arm A	Hypercholesterolaemia	LDL	Statines
	
	Anaemia	haemoglobin	ferro medication
	
	Rheumatic complaints	Waaler-Rose	NSAIDs
	
	Urinary tract infections	Urinary cultures	Antibiotics
	
	Prostate complaints	PSA	α-blockers

Arm B	Type 2 Diabetes Mellitus	HbA1c	Metformin
	
	Dyspepsia	gastroscopy	proton-pump inhibitors
	
	Chlamydia infections	chlamydia cultures	Antibiotics
	
	Thyroid problems	TSH	Levothyroxine
	
	Perimenopauzal complaints	FSH	Estradiol

For a complete list of all tests and drugs for the modules [See additional file 2]

**Figure 1 F1:**
[figure not shown]
**Flowchart of randomization and intervention**.

The Maastricht Medical Research Ethics Committee has approved this study. All participating GPs will be asked to sign a written informed consent form.

### Population

LQIC groups will be recruited by regional medical coordinators, which are regional health officers or managers often employed by regional hospitals or primary care laboratories. We have identified 24 organizations offering diagnostic facilities in the south of the Netherlands. All organizations will be visited by the researcher and asked to cooperate. Each medical coordinator then will be asked to recruit two to four LQIC groups. They will only be included when all group members consent to participate. The area from which groups can be recruited will be restricted to the three southern provinces of the Netherlands (Limburg, Noord-Brabant, and Zeeland) because these are covered by the insurance companies who provide data for the pharmaceutical database at Maastricht University (UM). A representative with special expertise in and knowledge of diagnostic testing, recruited by the medical coordinator, will attend each LQIC meeting. This representative will receive copies of the feedback forms of all GPs in a LQIC, to enable him or her to prepare the sessions. The representative will act as a moderator during the sessions devoted to diagnostics, after having been trained to do so (see under 'training'). The medical coordinator will finally also liaise between their diagnostic centre and the research team. Other stakeholders in our strategy include community pharmacists, UM, the DGV, insurance companies, PTAM groups, and individual GPs. Community pharmacists play a major role in PTAMs in the Netherlands, providing expertise and sometimes feedback on prescriptions to the participating GPs. Our intervention will leave the role of the pharmacists more or less unchanged. They provide easily accessible knowledge for GPs, thus breaking down barriers which might be inherent in distance support such as academic detailing. Like the medical coordinator, a pharmacist will function as a moderator in the LQIC. All community pharmacists will receive training prior to the first session, as described above. The pharmacists will receive copies of the feedback forms of all participating GPs in a group, to enable them to prepare the sessions.

The initiator of this trial is the Department of General Practice of Maastricht University. The design and maintenance of the database on diagnostics and the data gathering process are coordinated by the first author. The Maastricht University Centre for Information and Data Management (MEMIC) will host the diagnostics database, as they already do for the prescriptions database.

### Randomization

LQIC groups will be randomized as such (cluster randomisation). The intervention is aimed at these groups. Pre-randomization stratification will be performed on group size and level of group performance using a pre-randomization questionnaire [See additional file 1] prior to the intervention. The levels of group performance are as determined by DGV [28]. This level is a known confounder for an effective intervention on medical education among groups of GPs [30,31]. After stratification, all groups within a stratum will be randomly allocated to either arm A or arm B (Figure 1).

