The Dutch Institute for the Proper Use of Medicine (DGV) supports and initiates local or regional implementation of quality improvement projects on the use of drugs and supports local PTAM groups by supplying them with information and educational materials [28]. Performance levels of PTAM groups are assessed once a year and rated on the basis of four levels, level one being the poorest level of performance and level four the highest. We will use this division into levels as a parameter for pre-randomization stratification.

Participation in PTAM groups by GPs is facilitated by national and regional support organizations for primary care, as well as by the government and through incentives by insurance companies. Attendance at PTAM meetings is rewarded by accreditation. Currently, approximately 50% of the group meetings reach the desired level of performance described by policymakers [27]. To reach this level, groups must at least use feedback on prescribing, create working agreements, discuss barriers to change, and evaluate working agreements. Most groups are stable and remain together for 10 years or more, with members mostly being replaced gradually [27]. Because of the nature and stability of these groups, they provide an excellent and safe environment for participants to discuss their own behaviour and barriers to change. We expect this existing system of PTAM groups will ensure sustainability of the implementation itself. Therefore, we plan to use these groups in a large pragmatic trial on the implementation of guidelines, using the strategy previously tested by [name] *et al*. [7]. However, we will expand the strategy, using social interaction and external influencing as key approaches for establishing behavioural change, to both test ordering and drug prescribing. In our view, the groups will no longer function merely as a PTAM group, but rather begin acting as LQICs. This trial is expected to show whether the effects found in less pragmatic trials can be confirmed. Aiming at both test ordering and drug prescribing, our combination strategy could lead to an even larger effect because of synergy. We will also evaluate the costs of implementing the strategy on a large scale.

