### Explanatory variables

We will monitor data that are known to moderate quality assurance strategies. Therefore the following data will be gathered prior to the intervention: group size, age and gender of GPs, type of practice, number of patients registered with the practice, number of patients a GP is accountable for, number of working hours a week per GP, number of working hours a week for the group practice as a whole, distance to the hospital/diagnostic centre, responsibility for training GP trainees, total number of GPs collaborating in the practice, whether a GP admits sales representatives from pharmaceutical firms and if so how often, involvement in developing national guidelines, and GPs field(s) of special expertise.

All medical coordinators will be asked if problem-based test ordering forms are used in their region and to send us a copy of such a form.

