### Measurements

Prior to randomization, the chair of the group will be asked to fill out a short pre-randomization form, with which we will be able to determine the number of GPs in the group and be able to assess the level of group performance [See Additional file 1]. Data on test ordering and prescribing behavior will be extracted from the existing databases at baseline (t = 0) and t = 6 months, t = 12 months and t = 18 months. The dataset obtained at t = 0 and the final set will be used for a before-after analysis. A new questionnaire will be sent to the chair, assessing the level of group performance after the intervention. After each meeting, the chair will be asked to fill out a form with questions about the structure of the session, whether working agreements were created, whether barriers to change were discussed and if so what the nature of these barriers was, what educational materials were used, and the group members' experiences with the strategy.

The process of implementing the strategy in the south of the Netherlands will be monitored. Participants will be questioned about their experiences with the strategy. Participating GPs will be asked to report their experiences with the strategy, and to provide us with the necessary details on the sessions they have attended. After each session, the targets set by each group will be recorded.

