### Analysis

Analysis will be based on the intention-to-treat principle. Data on GPs lost to follow-up will be extracted from the various databases if possible.

We will analyse covariance using test and drug volumes during the intervention period as the dependent variables, and the baseline data and the explanatory variables as independent variables. The analysis will be repeated using proportions stemming from prescription performance indicators, if available. The unit of allocation to the trial is the LQIC. In larger practices with more than one GP, not all volumes of tests ordered and drugs prescribed will be traceable to an individual GP. In these cases, the unit of analysis will be the practice as a whole. Because of this unit of analysis error, the data will be analysed using multilevel modelling. Data on drugs and tests will be clustered to individual GPs at level one, the practice at level two, the LQIC at level three and the region at level four.

The nature of this study makes it difficult to blind the participants, except for the tests or drugs serving as controls in the other arm. The data analyst will be blinded for the allocation result. Costs of the intervention will be calculated. A cost-effectiveness analysis will be based on these figures. We will use cost minimization analysis from a societal perspective, assuming that the strategy will reduce redundant testing and prescribing. If there are signs of improvement of care (higher scores on the performance indicators), the impact on health may be estimated by modelling the future gains and benefits. Data include costs of coordinating the strategy by the regional contact group, of preparing feedback reports and of chairing the GP groups. The costs of the entire test ordering strategy by [name] were €554.70 per GP per six months (three meetings). The major part of the cost of this strategy consisted of opportunity costs, *viz *the costs of the GPs' time spent attending the session. Because GPs were already attending these meetings and were financially compensated, it seems fair to ignore the opportunity costs. This results in costs of the test ordering strategy of €92.70. The gains obtained by improving test ordering behaviour were €301.00 per GP per six months. Introducing the test ordering strategy would save €208.30 (92.70 to 301.00) per GP per six months [33]. Because prescribing costs are higher, the cost reductions gained by reducing superfluous prescribing should also be higher.

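### Randomisation is stratified on level of group performance, but the covariates named for the effect model leave that level out

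*Protocol article*

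**What the plan says.** The Randomization section of the protocol article names two stratification factors: "Pre-randomization stratification will be performed on group size and level of group performance". It justifies the second one: "This level is a known confounder for an effective intervention on medical education among groups of GPs". The Background section, after describing the four performance levels, says the same: "We will use this division into levels as a parameter for pre-randomization stratification".

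The Analysis section describes an analysis of covariance on test and drug volumes, with "the baseline data and the explanatory variables as independent variables". The multilevel structure has GP, practice, LQIC and region as levels and no term for the randomisation stratum.

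The section headed Explanatory variables gives the list. It begins with "group size, age and gender of GPs, type of practice, number of patients registered with the practice" and goes on to further GP and practice characteristics. Level of group performance is not in it.

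The level is available before allocation. According to the Measurements section, the group's chair fills out a pre-randomisation form from which the researchers will know the number of GPs and "be able to assess the level of group performance".

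**The concern.** A trial should normally be analysed with the factors on which it was stratified. Stratified allocation makes the arms alike on the factor, so the real sampling variance of the arm difference falls. A model without the factor does not see this. It leaves the variance that the factor explains in the residual, reports a standard error that is too large, and tests below the nominal level. Here the model, followed as written, carries one stratifier and drops the one the authors single out as important.

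Two things are at stake. The first is some precision, in a trial of 44 to 50 randomised groups. The second is correction of residual imbalance. About 50 groups over four levels is 12 or 13 per level on average, before crossing with group size, and 10% dropout is expected, so balance on the level need not be exact.

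**Working it through.** **1. Comparing the sections**

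| Factor | Stratifier (Randomization) | Covariate (Explanatory variables, used in Analysis) |
|---|---|---|
| Group size | yes | yes |
| Level of group performance | yes | not listed |

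The level appears in three other roles: as a process outcome, in the hypothesis that successful implementation goes with group performance, and, as a gain in level, as a predictor of the effect. None of these adjusts the arm comparison for the pre-randomisation level.

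**2. Could the term for baseline data include it?** The Measurements section uses the word for volumes: "Data on test ordering and prescribing behavior will be extracted from the existing databases at baseline (t = 0" and at later time points. It describes the performance level separately, as coming from the chair's form. Group size comes from that same form and is nevertheless listed by name as an explanatory variable. The inclusive reading is therefore possible but strained.

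**3. Size of the effect.** The article gives no figure on this point to reproduce.

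Inputs:
- ICC 0.10 and mean group size 7 (Sample size section).
- Alpha 0.05 (Sample size section). Sidedness is not stated; two-sided is assumed.
- R2, the share of LQIC-level variance explained by the level after the other covariates: not given. Assumed 0.05, 0.10 and 0.20.

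Variance of an LQIC mean, with total variance set to 1:

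0.10 + 0.90/7 = 0.2286

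Share of this that lies at LQIC level:

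0.10/0.2286 = 0.4375

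Share of the LQIC-mean variance that the level removes: f = 0.4375 × R2. The ratio of reported to correct interval width is 1/√(1 − f). The actual type I error is 2 × [1 − Φ(1.96/√(1 − f))].

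| R2 (assumed) | f | Width ratio | Actual type I error |
|---|---|---|---|
| 0.05 | 0.0219 | 1.011 | 0.048 |
| 0.10 | 0.0438 | 1.023 | 0.045 |
| 0.20 | 0.0875 | 1.047 | 0.040 |

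This uses a normal approximation, equal group sizes and allocation balanced on the level. It ignores the practice and region levels. It also uses the planning ICC, because no residual ICC after baseline adjustment is given.

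**4. Direction, by simulation.** The set-up was 44 clusters, four equal strata, analysis of cluster means and 4000 runs. Here the explained share is a share of the whole cluster-mean variance, so it corresponds to f and not to R2.

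| Explained share of cluster-mean variance | Type I error, level omitted | Type I error, level included |
|---|---|---|
| 0 | 5.0% | 5.0% |
| 0.1 | 3.6% | 4.5% |
| 0.2 | 3.0% | 4.8% |

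The f values in step 3 (0.02 to 0.09) lie between the first two rows, as do the type I errors of 0.048 to 0.040. Including the level when it explains nothing costs almost nothing: power for an effect of one cluster-level SD is 89.3% with it and 89.6% without.

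**The case against.** **The article is condensed, and covariate lists are often settled in the analysis plan.** That would answer a complaint about missing detail. This point is different: the article fixes the covariates by reference to a named list, and that list omits a stratifier. The article does not say the list is exhaustive, so a fuller document may already include the level. The published wording would still need to match it.

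**The assumed R2 has no support in the article, and the model already adjusts for baseline volume.** This stands. The article links the level to how well the intervention works, which is closer to effect modification than to prognosis for volume. Each arm is the control for the other arm's topics, so on a given topic the level may act mainly in the exposed arm, and a main effect would then recover less. The gain could be at or below the low end of the range.

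**A reader might infer intervals 5-12% too wide and a type I error of 0.04-0.03.** Those figures come from putting R2 = 0.10-0.20 directly into 1/√(1 − R2), which gives 1.054-1.118. That treats the LQIC component as the whole variance of an LQIC mean. On the article's own ICC and group size it is about 44% of it.

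**A reader might infer from the word confounder that the estimate is biased.** Stratified randomisation prevents that in expectation. The two harms also partly exclude each other: tests are conservative because the level is balanced, so only residual imbalance remains to be corrected, and its size is unknown.

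**A reader might infer that the model is overloaded with weaker covariates for 44 to 50 clusters.** The article does not support this. It describes the listed data as known moderators of quality assurance strategies. Many are GP or practice characteristics, informed by roughly 308 to 350 GPs (44 × 7 to 50 × 7).

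**Conclusion.** The inconsistency is in the text: of the two stratification factors, the named covariates include group size and omit level of group performance. The consequence is modest and in the conservative direction, and it invalidates nothing. If the level explains 10-20% of LQIC-level variance, intervals are about 2-5% too wide and the true type I error is about 0.045-0.040; at 5% explained, intervals are about 1% too wide. These figures rest on an assumed R2, the planning ICC of 0.10, seven GPs per group and a two-sided 5% test. If the level predicts nothing beyond baseline volume, the loss is nil. The correction is still worth making, because it brings the analysis into line with the randomisation at practically no cost.

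**What to change.** In the Analysis section, or by an addition to the Explanatory variables list, state that the level of group performance recorded before randomisation enters the effect model as a fixed effect, beside baseline volume and group size, with the planned random levels unchanged. Specify the pre-randomisation level, so that it is not confused with the level reassessed after the intervention.

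The cost is a change of wording. The level is already on the pre-randomisation form, no further data or groups are needed, and as a four-category factor it uses three degrees of freedom at LQIC level. Whether the other listed covariates stay in the main model or move to a secondary one is for the trial team and is not part of this correction.

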### Sample size

A sample size calculation is not really possible beforehand, because it is not yet known what working agreements will be created and with respect to what tests or drugs. The specific targets, incorporated in working agreements will probably be based on extreme overuse or underuse of certain tests or drugs by some or all group members. It is possible, for instance, that the group will decide to eliminate a particular obsolete test or drug or create a working agreement to decrease or increase the mean volume of tests ordered or drugs prescribed by 20%, from 35% to 55%.

The sample size calculation used in this trial is as follows: to detect an improvement of 20% in a certain target between groups, assuming an ICC of 0.10 [5], an alpha of 0.05 and a beta of 0.1 and a mean group size of seven, 44 LQICs would be needed. Anticipating a dropout of 10%, we would need to recruit 50 groups. A population this large would account for approximately 900,000 registered patients.

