Many studies have tried to find evidence for effective implementation strategies to improve quality of care. A multifaceted clustered RCT by [name] *et al*. aimed at optimizing GPs' test ordering behaviour by means of local quality improvement collaboratives (LQICs), found a decrease of 8 to 12% in test volumes over a period of six months [7]. This strategy was tested using six topics for continuing medical education (CME). Other studies have tested several implementation strategies to improve test ordering and prescribing behaviour. Passive dissemination of guidelines or recommendations does not seem to influence test ordering behaviour. Audit and feedback have often been used and showed mostly a modest effect in terms of influencing test ordering or prescribing. The effect of audit and feedback on adherence to desired practice ranged from -10% to +68% (median +16%) [8-12]. In other studies, the introduction of a problem-based test ordering form proved to be a promising tool to improve test ordering [7,13-18]. Similar effects on volumes of tests ordered as those in the [name] study have been found for more or less similar multifaceted implementation strategies [19,20]. Small group peer review using direct individual feedback seemed to reduce inappropriate prescribing [12,21,22]. Lagerlov found a 6 to 13% improvement in adherence to guidelines for the prescription of anti-asthmatic drugs and antibiotics for urinary tract infections in an RCT using reflection on guidelines and prescription feedback in small groups [23].

The Cochrane Effective Practice and Organization of Care group (EPOC) systematically reviews studies on implementation strategies to improve quality of care. Their work has generated the general insight that multifaceted strategies are usually more effective than single interventions [12,24], although this was not entirely confirmed by an NHS HTA review by Grimshaw *et al*. [16]. The prevailing insight is that the effect of an intervention is larger when tailored strategies are used and when barriers to and facilitators of change are addressed.

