### Intervention

Several theories have been postulated on how change in healthcare can be accomplished, and how effective change strategies can work in implementation of innovation. In cognitive theories, professional behaviour is considered to result from rational processes and experiences from earlier caseloads. In social interaction theories, change of professional behaviour is thought to be strongly mediated by peers in a group, the strength of inter-individual ties within groups, the existence of opinion leaders, and how much the desired behaviour is consistent with, and fits in, everyday practice. In total quality management theories, the use of systematically gathered data is considered to be crucial to facilitate effective professional development. These data can then be used in plan-do-study-act cycles (PDSA cycles) to provide insight into displayed behaviour and help identify areas where improvement is possible. This leads to the description of targets. These theories may overlap or may be complementary. In implementation science, the use of these theories as a framework is considered obligatory [32]. This intervention therefore will be multifaceted and consist of audit, comparative graphical feedback, and small group work with peer review of each other's performance, discussion of barriers to change, reaching agreement on future policy, and testing the agreement. After randomization to arm A or B, each group can choose from the corresponding set of five clinical topics allocated to that arm, to decide which three topics they want to discuss. Two balanced sets of topics, one for each arm, have been defined by the researchers. Each set consists of three major topics, from which the group has to choose two, and two minor topics, one of which has to be chosen. Thus, each LQIC will be asked to complete the entire strategy for three clinical topics of their choice during the intervention period. They are free to schedule extra meetings on topics not included in this trial, but these meetings will not be included in the final analysis. Feedback on the topic under discussion will be sent to the medical coordinator (diagnostic feedback) or local community pharmacists (prescription feedback) two weeks prior to the test ordering or the prescribing session of the LQIC, together with the relevant educational materials (see under 'clinical topics'). The first session, which will last approximately 90 minutes, will address the diagnostic test ordering behaviour of the individual GPs and will have the structure described under 'session structure' (Table 2). During this session, the GPs will discuss their diagnostic test ordering patterns and relate them to the guidelines provided. Individual and group working agreements will be created after barriers to change have been discussed. The second session will have the same structure, but the subject for discussion will be physicians' prescribing performance. This session will end by creating group and individual working agreements about preferred medication. Barriers to change from an individual perspective will again have to be discussed. After this first topic has been completed, the cycle will be repeated, for a new topic, as shown in Table 3. At the start of this new cycle, the group will reflect on the previous agreements, and revise them if necessary. The working agreements will then be prepared for further dissemination in the practices. Each session will be chaired by a member of the LQIC itself. When test ordering is discussed, a local representative from the diagnostic centre will be present, while a local community pharmacist will be present when pharmacotherapy is discussed. They will act as moderators, not as chairpersons.

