The existing PTAM group structure in the Netherland is widespread and functions reasonably well. However the need to improve the functioning of these groups is clearly present. Our strategy is known to improve test ordering behaviour of GPs, but is not used widely. Transferring PTAM groups into LQICs gives us the opportunity to add a discussion on test ordering behaviour to existing discussions on prescribing by GPs in PTAMs. The constitution of LQICs therefore is not 'old wine in new bottles' but a completely new approach within existing structures.

Several methodological challenges were encountered when we designed this trial. First, individual GPs are known to choose topics for CME in which they already show good performance [36]. This might result in a 'ceiling effect', meaning that little or no improvement in test ordering or prescribing behaviour would be possible. However, because the LQIC will have to reach consensus on the clinical topics they choose, the risk of such a ceiling effect is probably not very great.

Second, using an implementation strategy on ten different clinical topics from which GPs can choose introduces challenges to the sample size calculation. We chose to leave the LQICs some freedom of choice with regard to the topics. All clinical topics are well-described in the national guidelines for each topic. We will use a set of 204 tests and drugs to generate feedback [See Additional files 2] [See additional file 3]. Because we do not know what agreements local groups will come to, and do not know beforehand what the desired direction for change is, sample size calculation is very difficult. Because we intend to improve care by using the national guidelines, we do not expect to decrease quality of care by this study. However, it is impossible to predict if change will be towards better care.

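### The sample size calculation makes no allowance for topic choice, so the stated 90% power (44 LQICs, beta 0.1) does not apply to a single clinical topic

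*Protocol article*

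**What the plan says.** The Sample size section first warns that a calculation is hardly possible because the working agreements are not yet known. As an example it offers an agreement to "decrease or increase the mean volume of tests ordered or drugs prescribed by 20%, from 35% to 55" per cent. It then gives one calculation, "to detect an improvement of 20% in a certain target between groups", "assuming an ICC of 0.10", with "an alpha of 0.05 and a beta of 0.1 and a mean group size of seven". The result is 44 LQICs, raised to 50 for 10% dropout.

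The Intervention section defines what each group works on. An arm's set holds "three major topics, from which the group has to choose two, and two minor topics, one of which has to be chosen". Each LQIC therefore works on three of five topics and serves as a control for the other arm's topics.

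Effect question 2 asks about variation and total volumes for specific clinical topics, compared with GPs who received the strategy on other topics. Under Effect evaluation, the outcomes are tied to each group's own agreements and chosen topics. The Analysis section names intention to treat and a multilevel analysis of covariance with baseline as a covariate.

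**The concern.** The formula puts all 44 LQICs, 22 per arm, into one comparison on one target. Under the topic rules an average major topic is worked on by two thirds of an arm and an average minor topic by half. A single test or drug cannot be the subject of agreements in more groups than chose its topic. The stated power therefore describes a contrast that the design produces only if every LQIC in an arm picks the same topic.

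At stake is how topic-level results are read. A reader told that the trial was sized with beta 0.1 could take a null result for one topic as fairly strong evidence against a 20-point change, when that comparison had clearly less power.

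**Working it through.** **Inputs.** From the Sample size section: 35% versus 55% (given as an example, taken here as the basis of the calculation), ICC 0.10, seven GPs per LQIC, alpha 0.05, beta 0.1. Assumed because not stated: two-sided test, 1:1 allocation, no baseline adjustment. Design effect = 1 + (7 − 1) × 0.10 = 1.6.

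**1. The plan's own figure.** With the usual two-proportion formula (pooled variance under the null):
- 90% power: 128 GPs per arm; 128 × 1.6 / 7 = 29.3 LQICs per arm, 58.5 in total, so 60 in equal arms. With unpooled variance the total is 57.0, so 58.
- 80% power: 96 GPs per arm; 96 × 1.6 / 7 = 21.9 per arm, 43.9 in total, so 44.

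The 44 is thus not reproduced at beta 0.1 but matches beta 0.2. Other variants at 90% also miss it: one-sided gives 48, continuity-corrected 63 to 64.

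**2. Power of 44 LQICs on one common target.** Effective n per arm = 22 × 7 / 1.6 = 96.25. SE = √[(0.35 × 0.65 + 0.55 × 0.45) / 96.25] = √(0.475 / 96.25) = 0.0703. Power = Φ(0.20 / 0.0703 − 1.96) = Φ(0.89) = 81%.

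**3. Choosers of one topic versus all 22 LQICs of the other arm.** Even choice within each class is assumed.
- Major: 22 × 2/3 = 14.7 LQICs, effective n 64.2. SE = √(0.2475 / 64.2 + 0.2275 / 96.25) = 0.0789. Power = Φ(0.58) = 72%.
- Minor: 22 × 1/2 = 11 LQICs, effective n 48.1. SE = 0.0866. Power = Φ(0.35) = 64%.

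**4. All 22 versus 22 on one topic, with no effect in non-choosers.**
- Major: 20 × 2/3 = 13.3 points, 35% versus 48.3%. SE = 0.0704. Power = Φ(−0.07) = 47%.
- Minor: 20 × 1/2 = 10 points, 35% versus 45%. SE at most 0.0703. Power about 30%.

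**5. Summary, with larger numbers analysed.**

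| LQICs analysed | Common target | Choosers, major / minor | All by arm, major / minor |
|---|---|---|---|
| 44 | 81% | 72% / 64% | 47% / 30% |
| 50 | 86% | 77% / 69% | 52% / 33% |
| 60 | 91% | 84% / 77% | 60% / 38% |

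The pooled formula gives values within 2 points of these. The last row shows that correcting beta alone would not restore 90% per topic.

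**The case against.** **The difficulty is disclosed.** The Sample size section and the Discussion both say that unknown agreements and free topic choice make the calculation very hard. This is true, and a reader should not infer that the authors overlooked the problem or stated that all groups would share one target. But the article still uses the calculation to set recruitment at 50 and nowhere says that the stated power fails to hold for a topic.

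**Per-topic testing is not fixed.** The first effect outcome is each group's own agreed targets. If these were pooled across topics, all LQICs would contribute and the loss would not arise in this form. That choice may sit in an analysis plan that is not shown. This stands, so the point is conditional: it concerns the topic-level answers that effect question 2 asks for.

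**The diluted figures may not match a planned analysis.** The intention-to-treat statement is followed only by GPs lost to follow-up, and two outcomes are limited to chosen topics. This also stands; the 47% and 30% describe one possible analysis.

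**The planned model adjusts for baseline.** Adjustment would raise every figure. The article gives no baseline correlation. Purely as illustration, if adjustment multiplies the SE by √(1 − r²), an assumed r of 0.5 gives chooser power of Φ(0.20 / (0.0789 × 0.866) − 1.96) = 83% (major) and, likewise, 76% (minor); r of 0.7 gives 94% and 90%. The loss relative to a common target remains, but the unadjusted levels are not the trial's actual power.

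**Two stronger readings are not supported.** A reader might set the 20 points against the earlier trial, which "found a decrease of 8 to 12% in test volumes over a period of six months", and compute power for 8 to 12 points. Those figures are changes in test volume, whereas 35% to 55% is a difference in percentage points, and the article gives no conversion. A reader might also infer a multiplicity problem over 204 tests. The article says "We will use a set of 204 tests and drugs to generate feedback"; it describes a feedback set and does not plan 204 significance tests.

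**Conclusion.** The point holds in conditional form. The stated calculation ignores topic choice, and its 90% power does not carry over to a single topic.

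Two separate causes should be kept apart. About 9 points (90% to 81%) come from 44 matching beta 0.2 rather than the stated 0.1. Topic choice then takes 81% to 72% or 64% among choosers, a further 9 to 17 points, or to 47% or 30% when all LQICs are compared by arm.

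These levels assume a two-sided test, equal arms, 44 LQICs analysed, no baseline adjustment and even choice within major and minor topics; the last pair also assumes no effect in non-choosers. Average uptake of 2/3 and 1/2 follows from the design if groups comply, but uptake of any one topic is unknown. Uneven choice only moves power between topics: at most two major topics and one minor topic per arm can have all 22 LQICs, and the remaining two would then have none. At 30% uptake of a topic, power would be about 47% for choosers and 13 to 14% by arm.

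This does not show that the trial as a whole is underpowered, since a pooled analysis is not excluded.

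**What to change.** In the Sample size section:
- State that 44 LQICs with beta 0.1 does not apply to a single topic or item. Restate the common-target power as about 81% for 44 LQICs (86% for 50).
- Add the per-topic figures for 44 and 50 LQICs, with their assumptions: even choice within class, two-sided, 1:1, unadjusted, and no effect in non-choosers for the by-arm figures.
- Note that baseline adjustment is expected to raise these levels by an amount not yet known.

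The cost is a few sentences and less favourable stated power. No extra groups or data are needed.

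A single pooled contrast over topics need not be required. The Discussion says the desired direction of change is not known beforehand, and the Clinical topics section does not say that the modules fix a direction for each item. Pooling all of an arm's topics would also be diluted by the two that each group did not choose. Whether to make such a contrast the main estimate is a trade-off for the trial team.
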